### Study endpoints

The primary endpoint of the Part 1 observational study is the proportion of patients who proceed to enrollment in the Part 2 interventional trial. Secondary endpoints include the rate of postoperative ctDNA MRD positivity, recurrence rates stratified by ctDNA MRD status, and recurrence rates according to digital pathology findings.

The primary endpoint of the Part 2 randomized trial is the 3-year DFS, defined as the time from the date of randomization to the date of first documented disease recurrence or death from any cause, whichever occurs first, with censoring at 3 years. The occurrence of second primary cancers will not be considered an event.

Secondary endpoints include 5-year overall survival (OS), defined as the time from the date of randomization to the date of death from any cause, with censoring at 5 years; 5-year DFS; treatment-related adverse events based on NCI-CTCAE v5.0; treatment compliance; and patient-reported outcomes, assessed using the EORTC QLQ-C30 questionnaire. Additionally, ctDNA dynamics—including clearance rate—will be assessed as exploratory endpoints.

### Statistical analysis

A total sample size of 236 patients (118 per arm) of the Part 2 study was calculated based on an assumed hazard ratio (HR) of 0.64 for 3-year DFS, providing 80% power with a two-sided alpha of 0.05, and accounting for a 10% dropout rate. This HR corresponds to an estimated 3-year DFS rate of 46.3% in the experimental arm and 30.0% in the control arm, reflecting a clinically meaningful and statistically significant absolute improvement of 16%.

Assuming uniform accrual over 3 years and a minimum follow-up of 3 years for the last enrolled patient, a total of 159 DFS events is required. One interim efficacy analysis is planned after 30% of events have occurred. Sample size estimation was performed using the rpact package in R (version 4.1.1).

Survival outcomes (DFS and OS) will be analyzed using the Kaplan–Meier method and compared between treatment groups using the stratified log-rank test, with stratification factors identical to those used at randomization. Treatment effects will be estimated using a stratified Cox proportional hazards model to calculate the HR and its corresponding two-sided 95% confidence interval (CI).

Efficacy analyses for Part 2 will be performed primarily using the Full Analysis Set (FAS), defined as a modified intention-to-treat (mITT) population that includes all randomized patients who have received at least one dose of the investigational product, in accordance with the ITT principle. Patients will be excluded from the FAS if they (1) do not meet key eligibility criteria, (2) have not received any investigational product, or (3) have not undergone at least one post-randomization assessment.

Sensitivity analyses will be conducted on the Per Protocol Set, a subset of the FAS that includes patients who adhere to the protocol. Safety analyses will be based on the Safety Set, defined as all patients who received at least one dose of the investigational product.

At the time of study design, large-scale data on postoperative ctDNA positivity rates and long-term survival outcomes by MRD status in colon cancer were limited. Accordingly, key design parameters, including the initial sample size, were based on short-term data. As external and internal evidence accumulates, an interim analysis is planned to (1) assess the validity of the assumptions used for the initial sample size calculation and (2) determine whether sample size re-estimation is necessary. The interim analysis will evaluate the primary endpoint (DFS) and safety, and specific procedures will be outlined in the Statistical Analysis Plan, version 1.2 (July 2025). This analysis will be conducted once at least 48 DFS events (30% of the planned 159) have occurred.

For all other analyses, statistical significance will generally be declared at a two-sided *p*-value < 0.050.

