**Methods:**

This multi-center platform trial (NCT05534087) consists of a prospective observational study (Part 1) and an interventional randomized trial (Part 2). In Part 1, approximately 1,200 patients with colon cancer will be screened for MRD at 3–6 weeks postoperatively using a tumor-informed, hybrid-capture-based ctDNA MRD assay that tracks up to 100 patient-specific somatic variants identified through tumor whole-exome sequencing.

Key eligibility criteria includes: age ≥ 19 years, ≤ 6 weeks post-curative resection, pathological diagnosis of colon adenocarcinoma, stage III or stage II with high-risk features requiring adjuvant chemotherapy with FOLFOX/CAPOX, and no macroscopic residual disease. All patients in Part 1 will complete 3 months of standard adjuvant FOLFOX/CAPOX while awaiting MRD results. Patients with MRD positivity will be screened for the Part 2 clinical trial following the completion of the initial 3 months of treatment titled “*Randomized Controlled Phase III Trial of Treatment Intensification in Stage II–III Colon Cancer Patients with Positive MRD after Curative Resection.*” MRD-negative patients are managed at the investigator’s discretion.

Part 2 investigates the superiority of an experimental arm (modified FOLFIRINOX for 3 months) compared to a control arm (FOLFOX/CAPOX for 3 months). The primary endpoint of the Part 2 randomized trial is the 3-year disease-free survival (DFS), while secondary endpoints include the 5-year overall survival, 5-year DFS, treatment-related adverse events, treatment compliance, and patient-reported outcomes. A total of 236 patients will be enrolled and randomized in a 1:1 ratio, assuming a hazard ratio of 0.64, 80% power, a two-sided alpha of 0.05, and a 10% dropout rate.

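### The 159 DFS events and 236 patients assume 3 to 6 years of DFS follow-up, but the primary endpoint is censored at 3 years: about 131 to 146 events are expected, with 72% to 77% power instead of 80%

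*Protocol article*

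**What the plan says.** All references are to the protocol article.

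- **Study endpoints.** The primary endpoint of Part 2 is called 3-year DFS but is defined as a time-to-event variable, from randomization to recurrence or "death from any cause, whichever occurs first, with censoring at 3 years". 5-year OS is built the same way, with censoring at 5 years. 5-year DFS is a separate, secondary endpoint.
- **Procedures and interventions.** Recurrence surveillance in Part 2 covers the first three years after randomization. Patients then move to long-term follow-up, with survival checked every 6 months.
- **Statistical analysis.** The design rests on an "assumed hazard ratio (HR) of 0.64 for 3-year DFS", "providing 80% power with a two-sided alpha of 0.05", and 10% dropout. The hazard ratio is tied to an "estimated 3-year DFS rate of 46.3% in the experimental arm and 30.0% in the control arm". The result is "A total sample size of 236 patients (118 per arm) of the Part 2 study". Accrual is uniform over 3 years, with "a minimum follow-up of 3 years for the last enrolled patient, a total of 159 DFS events is required". DFS is compared by a stratified log-rank test and a stratified Cox model.
- **Interim analysis (same section).** It takes place "once at least 48 DFS events (30% of the planned 159) have occurred". It is to check the sample size assumptions and decide whether re-estimation is needed.
- **Abstract, Methods.** The same design is repeated, "assuming a hazard ratio of 0.64, 80% power, a two-sided alpha of 0.05, and a 10% dropout rate".

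**The concern.** If accrual lasts 3 years and the last patient is followed for 3 years, the first patient is followed for 6. A sample size computed on that timeline credits every patient with 3 to 6 years in which an event can count. The endpoint definition gives every patient exactly 3 years. Events after year 3 would be part of the 159 but not part of the primary analysis.

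Log-rank power is governed by the number of events. If the target includes events that the endpoint excludes, the confirmatory comparison has less power than stated even when every design assumption is exactly true. The interim information fraction, expressed against 159, shifts with it. Type I error and the validity of the comparison are not affected.

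**Working it through.** **Inputs (Statistical analysis section):** HR 0.64; two-sided alpha 0.05; power 80%; 3-year DFS 30.0% control and 46.3% experimental; 1:1 allocation; 236 patients; 10% dropout; 3 years of uniform accrual; 3 years of minimum follow-up; 159 events; interim at 48. **From Study endpoints:** censoring at 3 years.

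**Step 1: reproduce the event target.** Schoenfeld: d = 4(1.960 + 0.842)² / (ln 0.64)² = 157.6, so 158. The plan has 159. The extra event would fit a small inflation for the interim look, which is an assumption. At 159 events the power is 80.3%.

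**Step 2: reproduce 236.** Assume exponential DFS. The control hazard is −ln(0.30)/3 = 0.4013 per year, and the experimental hazard is 0.64 × 0.4013 = 0.2569. For follow-up uniform between 3 and 6 years, the event probability is 1 − (e^(−3λ) − e^(−6λ))/(3λ):

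- control: 1 − (0.300 − 0.090)/1.204 = 0.826
- experimental: 1 − (0.463 − 0.214)/0.771 = 0.677
- mean: 0.7515

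Then 159/0.7515 = 211.6, so 212 evaluable, and 212/0.9 = 235.6, so 236. The stated sample size is recovered with no 3-year cap and with dropouts removed entirely.

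**Step 3: apply the 3-year censoring.** The probability of an event by year 3 follows from the stated rates without any model: 1 − 0.300 = 0.700 and 1 − 0.463 = 0.537, mean about 0.6186. For 10% exponential loss over 3 years, the loss hazard is μ = −ln(0.9)/3 = 0.0351. The event probability is λ/(λ+μ) × (1 − e^(−3(λ+μ))), which gives 0.671 and 0.513, mean 0.592.

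**Step 4: events and power.** Power = Φ(|ln 0.64| × √d / 2 − 1.960), with |ln 0.64| = 0.4463.

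| Dropout handling | Expected events d | Power by formula | Power by simulation | 48/d |
|---|---|---|---|---|
| 10% removed (212 evaluable) | 212 × 0.6186 = 131 | 72.4% | 72.4% | 36.6% |
| 10% exponential loss over 3 years | 236 × 0.592 = 140 | 75.1% | 75.3% | 34.3% |
| No loss | 236 × 0.6186 = 146 | 76.9% | 77.1% | 32.9% |
| As stated | 159 | 80.3% | – | 30.2% |

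The simulation used 6,000 log-rank replicates per row. The proportion of runs reaching 159 events under the cap was 0, 0.6% and 4% in the first three rows.

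**Step 5: size of the gap in other terms.** About 159 − 131 = 28 of the planned events fall after year 3. With 131 events, 80% power corresponds to HR = exp(−2 × 2.802/√131) = 0.61. To expect 159 events under the cap would take 159/0.6186 = 257 evaluable patients, or 257/0.9 = 286 randomized.

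**The case against.** **The label.** 3-year DFS may be only a milestone name, with the log-rank test meant to use all follow-up. The text does not read that way: it states a censoring time, uses the same construction for 5-year OS, and lists 5-year DFS separately. If it is only a label, the endpoint definition is what needs correcting.

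**Re-estimation.** The trial plans to revisit its sample size and was still enrolling in April 2025 (116 of 236). This stands in part, since re-estimation could restore the power. But its stated purpose is to test the assumptions, and the shortfall is present when the assumptions hold. It does not make the two statements agree.

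**Dropout.** Removing 10% of patients entirely is pessimistic for a time-to-event analysis, because patients lost late contribute until they are lost. This stands, and 72% is the low end of a range. However, the same handling is what produces 236, and even with no loss the expected count is 146.

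**Stronger readings that the document does not support.**

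- A reader might infer that 159 events can never be reached. The shortfall is in expectation under the plan's own assumptions; higher event rates than assumed could still yield 159.
- A reader might infer that the final analysis would never be triggered. The document nowhere ties the final analysis to 159 events, and the minimum follow-up fits a calendar cut-off equally well.
- A reader might call the 30% interim fraction a separate mistake. 48/159 is 30.2% and correct as written; it shifts only because the total does.

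**Conclusion.** The sample size calculation and the primary endpoint definition contradict each other. Under the design's own rates, 236 patients are expected to yield about 131 to 146 primary events, and power at HR 0.64 is about 72% to 77%. That is roughly 3 to 8 percentage points below the stated 80%. The interim would fall at about 33% to 37% of the expected events.

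The capped counts of 131 and 146 rest only on the stated 3-year rates. The 140 and the reproduction of 236 also assume exponential DFS. The close match to 236 is strong evidence, but not proof, that uncapped follow-up was used. The power figures assume proportional hazards and a single test at two-sided 0.05; alpha spent at the interim efficacy look would lower them slightly.

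**What to change.** Choose one option and make the Abstract, Study endpoints and Statistical analysis sections agree, along with the SAP. The choice should be made before any interim DFS results by arm are seen.

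**(a) Keep the 3-year censoring.** Restate the expected events as 131 to 146 according to the dropout assumption, and power as 72% to 77% at HR 0.64 (80% at about HR 0.61 with 131 events). Recompute the interim fraction, and state that the final analysis takes place when the last patient reaches 3 years. The cost is wording and a less favourable stated power, with no extra patients. If re-estimation is used to recover 159 events under the cap, the figure to work from is about 286 randomized.

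**(b) Keep 159 events.** Remove the 3-year censoring from the primary log-rank and Cox analysis, report the 3-year Kaplan–Meier rate as the milestone, and record recurrence dates until the cut-off at the 6-monthly contacts already planned. The cost is an amendment to the primary endpoint definition and added data collection. The downside is that recurrence would be ascertained less intensively after year 3 than before it, and the analysis plan should acknowledge this.

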
### Procedures and interventions

In Part 1, patients undergo ctDNA MRD testing (CancerDetect™, IMBdx Inc.) using 20 mL whole-blood sample collected 3–6 weeks after surgery [10, 14–16]. Whole-exome sequencing (WES) of the surgical tumor tissue and matched white blood cells is first performed to identify patient-specific somatic mutations. Based on these findings, a personalized target capture panel comprising up to 100 variants is designed. ctDNA MRD testing is then conducted by high-depth sequencing of postoperative plasma DNA using this customized panel.

All enrolled patients initially receive 3 months of standard chemotherapy (FOLFOX/CAPOX). MRD test results will be disclosed to investigators and study participants within 3 months of initiating chemotherapy. For MRD-negative patients identified after completing the initial 3 months of standard chemotherapy, the decision to continue with an additional 3 months of chemotherapy (to complete a 6-month course) or to stop after 3 months will be left to the investigator’s discretion. MRD-positive patients will be screened for participation in Part 2 of the study after completion of the 3 months of chemotherapy. A total of 236 MRD-positive patients will be randomized 1:1 to receive either intensified chemotherapy (3 months of mFOLFIRINOX) or continued standard chemotherapy (an additional 3 months of FOLFOX or CAPOX).

The mFOLFIRINOX regimen consists of oxaliplatin (85 mg/m^2^), leucovorin (400 mg/m^2^), irinotecan (150 mg/m^2^), and 5-fluorouracil (2,400 mg/m^2^ for 46 h as a continuous infusion). The first dose of the clinical trial treatment is recommended to be administered on the scheduled start date of the next cycle of adjuvant chemotherapy—cycle 7 for FOLFOX or cycle 5 for CAPOX—and must be given within 3 weeks following randomization. Administration within + 7 days from Day 1 of each treatment cycle is permitted.

Stratified randomization was employed using mixed block sizes of 2 and 4 within each stratum. Patients are assigned through the web-based clinical trial platform system called Mytrial. The stratification factors were:•Risk group: high-risk (stage III colon cancer with T4 and/or N2) vs. low-risk (stage III without T4/N2 or stage II colon cancer)•Adjuvant chemotherapy regimen: FOLFOX vs. CAPOX•Study site

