## Discussion

This study was registered at ClinicalTrials.gov (NCT05534087), with a registration date of September 9, 2022. This study has been ongoing since December 2022 across 11 Korean Cancer Study Group (KCSG) institutions. As of April 2025, 701 of the planned ~ 1,200 subjects have been enrolled in Part 1, and 116 of 236 subjects have been enrolled in Part 2.

In our study, we employed the modified FOLFIRINOX regimen as an intensification strategy. FOLFIRINOX is a combination chemotherapy regimen comprising three key agents—5-fluorouracil, oxaliplatin, and irinotecan—commonly used in the treatment of colorectal cancer. A similar regimen, FOLFOXIRI plus bevacizumab, demonstrated significantly improved response rates, progression-free survival, and OS compared to sequential doublet therapies (FOLFIRI or FOLFOX plus bevacizumab) in the phase III TRIBE and TRIBE2 trials [17, 18]. These results established FOLFOXIRI as a standard treatment option in metastatic colorectal cancer, particularly in patients with poor prognostic features [1, 19].

Beyond the metastatic setting, mFOLFIRINOX has shown clinical benefit in locally advanced rectal cancer. In the phase III UNICANCER-PRODIGE 23 trial, 3 months of neoadjuvant mFOLFIRINOX significantly improved pathological complete response rates, 3-year DFS, and 3-year metastasis-free survival compared to standard therapy [20]. Although triplet regimens were associated with increased rates of adverse events—such as diarrhea, mucositis, neutropenia, and febrile neutropenia—these toxicities were manageable and did not increase treatment-related mortality.

mFOLFIRINOX has also demonstrated efficacy in the adjuvant setting. In the PRODIGE 24/CCTG PA.6 trial, it significantly improved both DFS and OS compared to gemcitabine monotherapy in patients with resected pancreatic cancer [21], further supporting its use as an effective adjuvant regimen.

Based on this body of evidence, we consider mFOLFIRINOX a rational intensification strategy for patients with stage II–III colon cancer and molecular evidence of MRD following curative resection.

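### The primary log-rank test is stratified by study site as well as risk group and regimen (up to 44 strata for 236 patients), and the stated 80% power makes no allowance for the information this loses

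*Protocol article*

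**What the plan says.** All of this is in the protocol article.

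- **Randomization** (Procedures and interventions): permuted blocks of 2 and 4 within strata. The factors are risk group (T4 and/or N2 stage III against the rest) and, as the list ends, "Adjuvant chemotherapy regimen: FOLFOX vs. CAPOX•Study site".
- **Number of sites** (Discussion): the trial runs "across 11 Korean Cancer Study Group (KCSG) institutions".
- **Primary test** (Statistical analysis): DFS and OS are "compared between treatment groups using the stratified log-rank test, with stratification factors identical to those used at randomization". The next sentence takes the HR and its 95% CI from a stratified Cox model. It does not repeat the factors, but the same ones are the natural reading.
- **Sample size** (Statistical analysis): "A total sample size of 236 patients (118 per arm) of the Part 2 study" rests on an "assumed hazard ratio (HR) of 0.64 for 3-year DFS, providing 80% power with a two-sided alpha of 0.05", with 10% dropout, 3 years of uniform accrual, at least 3 years of follow-up and 159 DFS events.

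The sample size text does not mention stratification, and the article states no rule for pooling small sites or sparse strata.

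**The concern.** A stratified log-rank test compares patients only with others in the same stratum. Once everyone still at risk in a stratum belongs to one arm, later events there contribute nothing to the statistic or its variance. With a handful of patients per stratum, most of whom are expected to have an event, this happens often. The usual event formula assumes that every event contributes close to one quarter to the variance, and that fails with many small strata.

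What is at stake is power and precision. A true HR of 0.64 would be missed more often than the stated 20%, and the confidence interval for the HR would be wider than the event count suggests.

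**Working it through.** **Inputs from the protocol article (Statistical analysis, unless noted).** HR 0.64; two-sided alpha 0.05; power 80%; "estimated 3-year DFS rate of 46.3% in the experimental arm and 30.0% in the control arm"; 10% dropout; 3 years of accrual and 3 years of minimum follow-up; 159 events; 236 patients. Strata come from Procedures and interventions, and the 11 sites from the Discussion.

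**1. Reproduce the plan's figures.**
- Events (Schoenfeld): 4(1.960 + 0.842)² / (ln 0.64)² = 157.6, so 158 against 159 stated. Allowing for an O'Brien-Fleming look at 30% of events leaves this at about 158.
- Power at 159 events: Φ(0.4463 × √(159/4) − 1.960) = 80.3%.
- Patients: exponential DFS at 30.0% and 46.3% at 3 years, averaged over 3 to 6 years of follow-up, gives an event probability of 0.751. Then 159/0.751 = 212, and 212/0.9 = 236.

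Both published figures therefore follow without any allowance for strata.

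**2. Count the strata.** 2 × 2 × 11 = 44. On average 236/44 = 5.4 patients and 159/44 = 3.6 events each. This is a ceiling: about 30 to 44 strata are occupied, depending on how uneven the sites and factors are.

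**3. Simulate the planned test.** 236 patients, 11 sites, blocks of 2 and 4 within each stratum, HR 0.64, 10% exponential dropout, analysis at 159 events unless stated, 6,000 to 12,000 runs per scenario (standard error about 0.4 to 0.6 points). Site sizes, factor splits and prognostic effects are **assumptions**, because the article does not give them. Effective events are four times the mean log-rank variance.

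| Scenario | Power, 4 strata | Power, all strata | Loss (points) | Effective events, 4 → all |
|---|---|---|---|---|
| Equal sites, 50/50 factors, not prognostic | 78.9% | 69.7% | 9.2 | 152 → 124 |
| Uneven sites, 20% FOLFOX, not prognostic | 79.5% | 72.1% | 7.4 | 152 → 129 |
| Very uneven sites, 10% FOLFOX, not prognostic | 78.4% | 73.2% | 5.2 | 152 → 134 |
| Uneven sites, not prognostic, follow-up to 6 years | 81.1% | 73.7% | 7.4 | 159 → 133 |
| Equal sites, risk-group HR 2 | 78.6% | 70.1% | 8.5 | 151 → 122 |
| Uneven sites, risk HR 2, site SD 0.3 (log hazard) | 75.7% | 70.3% | 5.4 | 150 → 125 |
| Uneven sites, risk HR 2, site SD 0.5 | 71.1% | 69.9% | 1.2 | 149 → 123 |
| 3-year censoring, equal sites, not prognostic | 74.5% | 67.7% | 6.8 | 136 → 118 |
| 3-year censoring, uneven sites, risk HR 2 | 74.7% | 68.0% | 6.7 | 136 → 119 |

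Other layouts extend these ranges. The loss is up to about 11 points with non-prognostic factors, about 5 to 8 at risk HR 1.5 with site SD 0.2, and about 0 to 2.5 at site SD 0.5.

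**4. Cross-check by formula.** In the non-prognostic runs at 159 events, about 19 to 27 of some 158 events fell where only one arm was at risk. Putting the effective events into the power formula:
- 124 events: Φ(0.4463 × √31 − 1.960) = 70.0%
- 134 events: Φ(0.4463 × √33.5 − 1.960) = 73%

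Both agree with the simulated power. Relative information is 124/152 = 0.82 to 134/152 = 0.88 in these rows, and the loss is 11 to 20% over all scenarios.

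**5. Type I error.** Under the null, the fully stratified test rejected in 5.0% of runs.

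**The case against.** - **Analysing as randomized is conventional, and leaving out a prognostic factor also costs power.** This stands in part. With site SD 0.5 and risk HR 2, the 4-stratum test itself has only about 71% power, and dropping site gains almost nothing. The Discussion cites evidence that T4/N2 features stay prognostic regardless of MRD status. That is a reason to keep risk group as a stratum, and the 4-stratum analysis does. It says nothing about site.
- **The loss depends on facts the article does not give.** This stands. A reader might infer a fixed loss of 7 to 11 points. That is the upper part of the range and needs factors with little prognostic effect and patients spread over many strata.
- **Forty-four is a ceiling.** This also stands. Large sites would carry most of the information, and very uneven sites reduce the loss to about 5 to 6 points.
- **The unseen statistical analysis plan may pool small sites.** It may, and the absence of a pooling rule from a condensed article is not held against the plan. The article nevertheless states positively that the factors are identical to those at randomization. If the analysis plan pools, the two texts differ and need reconciling.
- **A reader might infer that the primary test is invalid.** It is not: its type I error is 5%.
- **A reader might attribute the whole shortfall under 3-year censoring to the strata.** With DFS censored at 3 years there are about 140 events, and even the unstratified test has only about 75% power. That part comes from the censoring, not from site.

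**Conclusion.** The point holds as one of power and precision, and it should be fixed. The stated 80% belongs to a test with few or no strata, whereas the test the article specifies has up to 44. With follow-up as in the sample size calculation, the specified test has about 69 to 74% power in the scenarios examined, against 71 to 82% with risk group by regimen strata.

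The loss due to site is about 7 to 11 points if the factors are not prognostic (5 to 6 if sites are very uneven), about 5 to 8 with moderate effects, and near 0 to 2.5 with strong site effects. With 3-year censoring it is about 0 to 8 points; the rest of the shortfall from 80% there comes from the censoring or the prognostic effects.

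The strata count and the absence of an allowance follow directly from the article. The size of the loss rests on assumed site sizes, regimen and risk mix, and site effects. Dropping site gained power or roughly broke even in every scenario.

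**What to change.** Stratify the primary log-rank test and the Cox model by risk group and regimen only (4 strata). Keep site as a randomization factor and address it in a sensitivity analysis, for example a site frailty or a stratified analysis with small sites pooled. If site is to remain a primary stratum, restate the power, or the events required, for the fully stratified test and give the site sizes and factor mix assumed.

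The change is one sentence in the protocol and one in the analysis plan. It should be made before any unblinded DFS data from the interim analysis (planned at 48 events) are seen, so that the choice of strata cannot be linked to results. The cost is that one randomization factor is missing from the primary model, which gives up little or nothing unless site effects are very strong.

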## Methods

### Study aim and design

This multi-center, prospective, open-label, platform trial consists of two sequential parts: a prospective observational study (Part 1) and a randomized controlled phase III clinical trial (Part 2) (Fig. 1). Part 1 involves screening approximately 1,200 patients for MRD using postoperative ctDNA analysis, while Part 2 evaluates the efficacy of intensified chemotherapy (3 months of FOLFOX or CAPOX followed by 3 months of mFOLFIRINOX) versus standard chemotherapy (6 months of FOLFOX or CAPOX) in MRD-positive patients identified in Part 1 (Fig. 2).

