For patients enrolled in Part 2, recurrence surveillance will be performed every 12 ± 4 weeks during the first 2 years following randomization, and every 24 ± 4 weeks during the third year. Surveillance will include carcinoembryonic antigen (CEA) testing, contrast-enhanced abdominal/pelvic CT, chest CT, and serial ctDNA MRD assessment using 20 mL whole-blood samples (Part 2, Fig. 3).

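### The primary efficacy set can drop randomized patients for reasons linked to arm and prognosis, and no stated efficacy analysis includes everyone randomized

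*Protocol article*

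**What the plan says.** Under Statistical analysis, the primary efficacy set is the FAS, described as a modified ITT population that "includes all randomized patients who have received at least one dose of the investigational product, in accordance with the ITT principle". The next sentence adds the exclusions: "Patients will be excluded from the FAS if they (1) do not meet key eligibility criteria, (2) have not received any investigational product", and a third group, those who "have not undergone at least one post-randomization assessment".

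On robustness, the same section says: "Sensitivity analyses will be conducted on the Per Protocol Set, a subset of the FAS that includes patients who adhere to the protocol". No other efficacy set is named.

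Four other statements bear on how these rules act:

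- Study aim and design: "This multi-center, prospective, open-label, platform trial consists of two sequential parts". The Abstract states that Part 2 tests superiority.
- Study endpoints: DFS runs from randomization to "first documented disease recurrence or death from any cause, whichever occurs first".
- Procedures and interventions: the first trial dose may be given up to 3 weeks after randomization.
- Procedures and interventions, on Part 2 imaging and laboratory follow-up: "recurrence surveillance will be performed every 12 ± 4 weeks during the first 2 years following randomization".

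**The concern.** The ITT principle means analysing every randomized patient in the assigned arm. A set defined by dosing, eligibility review and the presence of an assessment does not do that, so the section contradicts itself. Because the PPS is nested in the FAS, the sensitivity analysis cannot show what the exclusions did.

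The design gives the exclusions a route to depend on arm. Patient and investigator know the allocation before the first post-randomization dose, and up to 3 weeks may pass in between. A patient who declines the assigned arm in that interval leaves the primary analysis under the dosing rule. A patient who dies before any assessment has had a primary-endpoint event but, on the wording of the third rule, is removed. If such patients differ in prognosis from those who stay, and their number differs between arms, the hazard ratio is no longer protected by randomization.

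**Working it through.** **1. The plan's own figures.** With HR 0.64, two-sided alpha 0.05, 80% power and 1:1 allocation, Schoenfeld's formula gives 4 × (1.960 + 0.842)² / (ln 0.64)² = 157.6, so 158 events against the stated 159. With exponential DFS, 36 months of uniform accrual and 36 months of minimum follow-up, the mean event probability is 0.7515. Then 159 / 0.7515 = 211.6, and 211.6 / 0.90 = 235.1, rounded up to 236. The design reproduces, so the point concerns the analysis set and not the planned numbers.

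**2. Events by 3 years.** From the stated 3-year DFS rates (30.0% and 46.3%) and 118 patients per arm, without dropout:
- control: 118 × 0.700 = 82.6
- experimental: 118 × 0.537 = 63.4

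**3. Effect of removing early deaths (number removed is assumed).** A patient who dies early contributes almost no follow-up time, so the HR changes nearly in proportion to the event count.
- Two experimental-arm deaths removed: 0.64 × (63.4 − 2) / 63.4 = 0.62.
- Two control-arm deaths removed: 0.64 × 82.6 / (82.6 − 2) = 0.66.
- For scale, the standard error of ln HR is about √(1/63.4 + 1/82.6) = 0.167. The first shift is ln(61.4/63.4) = −0.032, roughly one-fifth of a standard error.

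**4. Effect of one-sided exclusion under no true effect (rates and hazards are assumed).** Log-rank simulation, 118 per arm, 4,000 runs per scenario, with patients excluded from the experimental arm only:

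| Share of that arm excluded | Hazard of excluded relative to the rest | Apparent HR | One-sided error (nominal 2.5%) |
|---|---|---|---|
| 5% | 1 | 1.00 | 2.8% |
| 5% | 2 to 3 | 0.97 to 0.96 | 3.9% to 4.3% |
| 10% | 1 | 1.00 | 2.4% |
| 10% | 2 to 3 | 0.94 to 0.92 | 6.7% to 7.5% |

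With average prognosis (relative hazard 1) the results agree with no bias within simulation error, about √(0.025 × 0.975 / 4,000) = 0.25 percentage points. Excluding poor-prognosis patients from the control arm instead would push the HR the other way.

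**5. Power.** If a share of patients and the same share of the 159 events were lost, power would be 79.5% at 2%, 78.3% at 5% and 76.1% at 10%. Bias is the larger worry.

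**The case against.** The strongest reply is that few patients will be affected. Table 1 requires agreement to Part 2 at entry to Part 1 and excludes patients who refuse mFOLFIRINOX or are unsuitable for it. All of them have already had 3 months of an oxaliplatin doublet. The illustrated shift of 0.02 in the HR is small against sampling error. This stands as a limit on likely size. It does not repair the definition: agreement was given before the arm was known, and the plan neither states nor bounds the number excluded.

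Several stronger readings are tempting but not supported:

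- *That the third rule would delete all failures before the first surveillance visit.* At the planned hazards (control −ln 0.30 / 3 = 0.4013 per year, experimental 0.64 × 0.4013 = 0.2568), 118 × (1 − exp(−0.4013 × 12/52.18)) = 10.4 control and, likewise, 6.8 experimental patients have an event by week 12. These are not counts of exclusions. A documented recurrence is itself an assessment, so that patient stays in. Nor is the term limited to the surveillance scan; adverse-event, compliance or QLQ-C30 data might qualify. Only deaths before any assessment are at risk, and the article gives no rate for them.
- *That toxicity of the triplet drives removal.* A patient with toxicity has been dosed, and a recorded toxicity is arguably an assessment.
- *That investigational product leaves out the control arm.* This would empty that arm from both the FAS and the Safety Set, which cannot be intended. The wording needs a definition, no more.
- *That eligibility failures may be judged after outcomes are known.* The article is silent on timing, and the analysis plan may settle it.

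It is also true that censoring unassessed patients at randomization adds almost no information. The gain comes from counted deaths and from undosed or ineligible patients who have outcome data.

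**Conclusion.** The point holds in a limited form. The primary set is called ITT-compliant but applies three post-randomization exclusions, and the only sensitivity set sits inside it. In an open-label superiority trial these rules can bias the HR. A reader might infer that the bias favours mFOLFIRINOX; the document does not determine the direction.

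Nor can the size be derived, because no exclusion rates are given. The move from 0.64 to about 0.62 assumes two experimental-arm deaths dropped. The inflated error rates assume 5% to 10% one-arm exclusion at two to three times the hazard. With average-prognosis exclusions there is no bias. It should be fixed, but what can be shown does not mark it as a critical flaw.

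**What to change.** Define the primary efficacy population as all randomized patients analysed in the assigned arm. Count every recorded death or recurrence as an event, and censor at randomization only those with no assessment and no recorded death. Keep the present FAS and the PPS as sensitivity sets. For sets that depend on dosing, define investigational product as the first post-randomization dose of study treatment in either arm.

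The cost is a wording change in the protocol and the analysis plan, and slight dilution of the effect from including non-compliers. The 236 patients, 159 events and about 80% power do not change. The Discussion reports 116 of 236 patients enrolled in Part 2 by April 2025, and the interim DFS analysis is due at 48 events; the change is best made before DFS is compared by arm.
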